### Data Collection

Quantitative data will be collected automatically by the digital platform, recording referral time stamps, referral reason, urgency category, facility identifiers, bed availability status, and referral outcome. Preimplementation historical data will be extracted from paper registers at participating institutions. Health care professional surveys will be administered at 2 time points: within 2 weeks of deployment and at the end of the 6-month period. Patient surveys will be administered at the point of referral completion. Semistructured interviews will be conducted at midimplementation and at end of study. Focus group discussions will be held at approximately 3 months after deployment. Data quality will be checked through double-entry verification of a random 10% sample and monthly data monitoring committee reviews.

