## Introduction

Digital health has become a key facilitator of health care provision in low- and middle-income countries (LMICs), where resource scarcity, geographic challenges, and systemic inefficiencies restrict access to timely care [1]. Mobile health technologies serve as health system–strengthening tools supporting health care professional-to-health care professional communication, clinical decision-making, and coordination of patient care across levels of the health system [2]. Electronic referral (e-referral) systems specifically have been receiving growing interest as scalable solutions to delays and miscommunication that are inherent in paper-based referral pathways [3].

Emergency referral systems in Pakistan are still largely paper based and very fragmented. Timely and effective emergency referrals are especially critical for neurosurgical conditions—including traumatic brain injury, spinal trauma, and acute stroke—where delays of even a few hours can result in permanent disability or death [4]. The health care system is overstretched in Khyber Pakhtunkhwa (KP), a Pakistani province with a population of more than 40 million. The area is typified by a predominantly rural population, a history of conflict-related displacement, and a lack of health care infrastructure in peripheral regions [5].

High numbers of preventable referrals to tertiary care hospitals are regularly received by Lady Reading Hospital (LRH), Khyber Teaching Hospital (KTH), and Hayatabad Medical Complex (HMC). These unnecessary transfers are made without checking bed availability or specialist capacity, creating unnecessary patient transfers, increasing health care expenses, and exacerbating overcrowding in tertiary facilities [6]. This is further complicated by self-referred patients. At the same time, district-level facilities are underused due to the lack of resources and staffing, which leads to an imbalance paradox within a single provincial health system.

The fast growth of mobile and internet connectivity in Pakistan offers a favorable setting to digital health interventions. Mobile phone penetration grew to over 80% in 2022 as compared to less than 10% in 2000, with over 190 million cellular connections and over 124 million broadband subscribers registered in 2023 [7]. This online base offers a significant prospect to implement mobile-based referral systems even in rural and underserved areas of KP.

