## Methods

### Study Design

This is a mixed methods implementation study with a prospective cohort design for the quantitative component and a qualitative exploratory component. The quantitative component captures all emergency referrals recorded through the digital platform during a defined 6-month pilot period using preimplementation historical referral data from participating institutions for pretest-posttest comparison. The qualitative component examines health care provider and patient experiences through surveys, semistructured interviews, and focus group discussions. Quantitative and qualitative findings will be integrated using a convergent mixed methods framework.

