### Outcomes

Primary outcomes are change in the proportion of unnecessary referrals (defined as referrals where the receiving specialist determines that the patient could have been managed at the referring facility without transfer) and change in referral initiation–to-response time. Secondary outcomes are change in bed use, number of unanswered referral requests, referral acceptance and decline rates, number of cases managed through remote advice without transfer, patient mortality among emergency referrals where feasible, referral-related costs where feasible, patient and health care professional satisfaction, and platform usability (Table 2).

**Table 2 table2:** Outcome definitions, data sources, and analysis plan.

Outcome	Definition	Data source	Analysis plan
Change in unnecessary referral rate	Referrals deemed manageable at the referring facility without transfer	Platform records+specialist response field	Chi-square test and multivariable logistic regression
Change in referral initiation–to-response time	Interval from referral submission to specialist acknowledgment (min)	Platform time stamps	2-tailed *t* test or Mann-Whitney *U* test and multivariable regression
Change in bed use	Proportion of beds occupied at the receiving facilities	Platform dashboard+hospital records	Descriptive statistics and pretest-posttest comparison
Unanswered referral requests	Referrals without documented specialist response	Platform records	Frequency and rate calculation
Proportion of referrals answered within the urgency window	Percentage of referrals receiving a specialist response within predefined urgency-specific response targets	Platform time stamps	Frequencies, percentages, and chi-square test comparison
Referral acceptance and decline rate	Proportion of referrals accepted vs declined by the receiving facility	Platform records	Frequencies and chi-square test
Cases managed through remote advice	Referrals resolved via bidirectional specialist advice without transfer	Platform communication logs	Frequency and descriptive subgroup analysis
Patient satisfaction	Patient and attendant survey domain score	Structured survey (Multimedia Appendix 1)	Means and SDs and Likert distribution
Health care professional satisfaction and usability	Health care professional survey domain score	Structured survey (Multimedia Appendix 1)	Means and SDs and thematic integration

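### Both primary change outcomes are sourced only from platform fields, the comparator is pre-platform paper registers, and no common way of ascertaining either outcome in both periods is stated

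*Protocol article*

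**What the plan says.** Under Outcomes, both primary outcomes are changes: in the proportion of unnecessary referrals and in the time from referral initiation to response. A referral counts as unnecessary by a clinical judgment, namely "referrals where the receiving specialist determines that the patient could have been managed at the referring facility without transfer". Table 2 gives the data source of that outcome as "Platform records+specialist response field". Response time is the number of minutes from submission to specialist acknowledgment, with the source "Platform time stamps".

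The comparison period under Data Analysis is December 2025 to May 2026, the six months before deployment. Data Collection says of it: "Preimplementation historical data will be extracted from paper registers at participating institutions".

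On the pilot side, the quantitative component "captures all emergency referrals recorded through the digital platform during a defined 6-month pilot period", and Eligibility Criteria likewise admits only records created on the platform. Table 2 treats cases resolved by specialist advice without transfer as platform referrals.

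One other change outcome in Table 2, bed use, names a source outside the platform: "Platform dashboard+hospital records". Neither primary outcome does.

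**The concern.** A pre-post test needs the outcome measured in the same way, on the same kind of unit, in both periods. Here the stated source of each primary outcome did not exist in the first period, and the stated source for the first period is not listed against either outcome. The article does not say that the registers hold a specialist's view on whether the patient could have stayed at the referring facility, or request and response times to the minute. It gives no rule for deriving them.

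The unit may differ too. A platform record is a referral request, which may end in advice alone. What a register entry represents is not stated, and a request that never led to a transfer may leave no trace in a receiving hospital's register. If some referrals during the pilot are made outside the app, they are not in the cohort. Nothing states that use is mandatory or that the share captured will be measured.

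At stake are both primary conclusions. A difference, or the absence of one, could come from recording or from who used the app. The multivariable regression in Table 2 cannot separate these from the intervention, because instrument and period coincide exactly.

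**Working it through.** **Stated figure.** The only quantity in the article is the expected 5000 to 7000 records (Sample Size and Sampling). It is a volume estimate from the tertiary hospitals' logs, with no formula to reproduce.

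**Sources side by side.**

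| Outcome | Source named in Table 2 | Source named for the pre-period |
|---|---|---|
| Unnecessary referrals | Platform records and specialist response field | Paper registers; no field or rule given |
| Response time | Platform time stamps | Paper registers; no field or rule given |
| Bed use (secondary) | Platform dashboard and hospital records | Hospital records available |

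**How much a mismatch could matter.** The article gives no baseline rate, register accuracy or app coverage, so all of these are assumed. From the article: 5000 or 7000 records (taken here as the size of the pre-period) and a significance level of 0.05, used two-sided.

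Rejection probability = Φ[(d − 1.96·SE0)/SE1], where d is the absolute difference, SE0 = √[p̄(1−p̄)(1/n1+1/n2)] and SE1 = √[p1(1−p1)/n1 + p2(1−p2)/n2].

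*Precision.* With 5000 to 7000 records per period, 80% power is reached for differences of about 1.9 to 2.8 percentage points (baseline 20% to 50%). For response time, (1.96+0.84)·√(2/n) gives about 0.056 SD at 5000 and 0.047 SD at 7000. Small artefacts are therefore detectable.

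*Instrument difference only.* True rate 30% in both periods; the platform captures all unnecessary cases and registers a fraction s, with no false positives.
- s = 0.90: observed pre-rate 0.30 × 0.90 = 0.27. At n = 5000, p̄ = 0.285, SE0 = 0.00903 and SE1 = 0.00902, so (0.03 − 0.01770)/0.00902 = 1.36 and the probability is 0.91. At n = 7000 it is 0.98.
- s = 0.95: observed pre-rate 0.285; probability 0.38 (5000) or 0.50 (7000).

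This version produces a spurious rise. Registers that over-call unnecessary cases would produce a spurious fall.

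*Population difference only.* Overall rate 30% in both periods, app coverage c, off-app rate r. The platform rate is (0.30 − (1−c)·r)/c. The pilot sample is c times the pre-period sample.

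| c | r | Platform rate | Spurious change | Rejection probability (5000 / 7000) |
|---|---|---|---|---|
| 0.70 | 0.40 | (0.30−0.12)/0.70 = 0.257 | fall of 4.3 points | 0.99 / >0.99 |
| 0.70 | 0.20 | (0.30−0.06)/0.70 = 0.343 | rise of 4.3 points | 0.99 / >0.99 |
| 0.90 | 0.40 | (0.30−0.04)/0.90 = 0.289 | fall of 1.1 points | 0.22 / 0.29 |
| 0.90 | 0.20 | (0.30−0.02)/0.90 = 0.311 | rise of 1.1 points | 0.22 / 0.28 |
| 1.00 | any | 0.300 | none | – |

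*Remote-advice cases.* These are platform records and could meet the definition of unnecessary, since they were managed without transfer. If counted that way, with no counterpart in the registers, successful remote management would push the measured pilot rate up. The article does not say how they are counted.

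**The case against.** The article is a condensed document, and an abstraction rule for the registers could sit in a full protocol. That is fair as far as it goes. But the article does not leave the sources open: Table 2 states them, and it names hospital records for bed use while naming none for either primary outcome. A register rule held elsewhere would have to be reconciled with the table as printed.

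Several stronger readings are tempting and not supported:
- *Response time has no baseline at all.* The article does not say what the registers contain. It only fails to show that they contain these times.
- *Paper-era referrals were never acknowledged.* The Introduction says "These unnecessary transfers are made without checking bed availability or specialist capacity", but this is background about unnecessary transfers, not about referrals in general. That request and response times were often absent is an inference.
- *Referrals bypass the app during the pilot, while every register entry counts beforehand.* Neither is stated. Off-app referral is plausible, because nothing makes use mandatory and the limitations mention digital literacy and connectivity differences, but its extent is unknown.
- *The bias flatters the platform.* It can go either way, as the working shows, and the population part disappears at full coverage apart from remote-advice cases.

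The limitations section does concede that paper records may be incomplete. That is a different matter from measuring the outcome by another instrument or in another population.

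**Conclusion.** The point holds. As written, neither primary pre-post test has a stated common measurement across the two periods, and the populations may differ as well. The measurement half rests directly on the text of Table 2, Data Collection and Data Analysis. The population half depends on app coverage, which the article neither states nor plans to measure, and so is a risk of unknown size.

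No bias estimate can be drawn from the article. The figures in the working only show that modest mismatches, of about 1 to 4 points under the assumed rates, range from rarely to almost always significant at the planned volume, and that a larger census does not remove them. The matter should be settled before deployment, because both primary conclusions depend on it.

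**What to change.** 1. Before deployment, check whether the registers hold request and response times, and enough clinical information to judge whether the patient was manageable at the referring facility.
2. For the pre-post contrast, use the same source and the same written criteria in both periods. Continue the planned register extraction through the pilot months, so that referred arrivals are counted whatever the channel. Report app coverage. Report remote-advice cases separately and state how they enter the denominator, since a count of arrivals alone would leave them out and change what is being estimated.
3. If the registers lack the times, or cannot support the classification, remove the word change and the pre-post test for that outcome and report it as a description of the pilot period. For response time, that means by month and urgency class.
4. Amend the data-source column of Table 2 to match.

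A proxy based on what happened to the patient after arrival is an option only if labelled as a different outcome. It does not measure the referring facility's capability.

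The cost is protocol wording, additional register extraction during the pilot, and the possible loss of one or both pre-post claims.

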### Survey Instrument and Scoring

The structured survey instrument (Multimedia Appendix 1) comprises separate versions for health care providers and patients or attendants, covering usability, perceived efficiency, communication quality, referral safety, workload, and overall acceptability. Each domain contains 4 to 6 Likert-scale items (1=“strongly disagree”; 5=“strongly agree”). Domain scores are calculated as the mean of item responses.

### Interview and Focus Group Topic Guide

The semistructured interview and focus group discussion topic guide (Multimedia Appendix 2) covers 7 domains: platform usability, fit with clinical workflow, barriers to adoption, facilitators, perceived impact on referral decisions, bidirectional communication, and recommendations for scale-up.

### Data Analysis

Quantitative analysis will use SPSS (version 28; IBM Corp). Descriptive statistics, normality testing, pretest-posttest paired comparisons (2-tailed t test or Wilcoxon signed-rank test), chi-square or Fisher exact tests, and multivariable logistic regression will be conducted. A *P* value of less than .05 will be the significance threshold. Missing data will be handled using complete-case analysis (<10% missing) or multiple imputation (>10% missing). Historical referral data from participating institutions covering the 6 months immediately preceding platform deployment (December 2025-May 2026) will serve as the preimplementation comparison period.

Qualitative analysis will follow the six-step reflexive thematic analysis framework by Braun and Clarke [15]: (1) familiarization with the data, (2) generation of initial codes, (3) search for themes, (4) review of themes, (5) definition and naming of themes, and (6) production of the report. Interviews and focus group discussions will be audio recorded and transcribed verbatim prior to analysis. Two researchers will independently code the transcripts; coding disagreements will be resolved through discussion and consensus. Reflexive memos and an audit trail will be maintained throughout the analytical process. Recruitment will continue until thematic saturation is achieved.

Quantitative and qualitative datasets will first be analyzed independently, and results will subsequently be merged during the interpretation phase using a convergent mixed methods approach. Joint display matrices will be used to facilitate integration. Merged findings will be examined for convergence, complementarity, and divergence between the quantitative and qualitative strands.

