**Methods:**

A convergent mixed methods design will be employed, incorporating a quantitative prospective cohort study alongside a qualitative exploratory component. The quantitative arm will adopt a census-based methodology, enumerating all emergency referrals processed through the digital platform over a 6-month pilot period commencing June 2026, with preimplementation historical referral data serving as the comparator. An estimated 5000-7000 referral episodes are anticipated. Primary outcomes include reduction in unnecessary referral rates and referral-to-response time. Secondary outcomes encompass inpatient bed occupancy rates, unanswered referral proportions, case acceptance and declination rates, remotely managed cases precluding physical transfer, patient mortality indices where ascertainable, and health care provider satisfaction scores. Statistical analysis will be performed using IBM SPSS, incorporating descriptive statistics, chi-square, or Fisher exact tests, paired comparisons, and multivariate logistic regression. The qualitative component will comprise structured surveys, semistructured interviews, and focus group discussions among purposively sampled health care professionals and patients, with thematic analysis conducted independently by 2 coders and findings integrated via a convergent mixed methods framework.

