## Results

### Overview

This study received no external funding. As of manuscript submission, participant recruitment has not yet commenced because pilot deployment is scheduled to begin in June 2026. System development, stakeholder engagement, user-centered design, beta testing, and validation activities have been completed. Data collection is expected to continue through November 2026, quantitative and qualitative data analysis is planned for December 2026 through February 2027, and study findings are expected to be submitted for peer-reviewed publication in spring 2027. System development, user-centered iterative design, stakeholder engagement, beta testing, and validation have been completed. The pilot implementation phase is scheduled to commence in June 2026 across a phased sequence of participating facilities beginning with primary and secondary care hospitals and expanding to the 3 tertiary MTIs by July 2026. Data collection will continue for a 6-month period, with an anticipated sample of 5000 to 7000 emergency referral records. Qualitative data collection will begin at approximately 2 months following platform deployment and will continue until November 2026. Quantitative and qualitative data analysis is planned for December 2026 to February 2027.

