### Study Timeline

The study timeline is outlined in Table 3.

**Table 3 table3:** Study timeline.

Phase and activity	Time frame	Status
Phase 1: requirement gathering and stakeholder consultation	January 2026-February 2026	Completed
Phase 1: platform design, prototyping, and development	February 2026-May 2026	Completed
Phase 1: beta testing and iterative refinement	May 2026	Completed
Phase 1: validation testing and health care professional training	May 2026	Completed
Phase 2: pilot deployment and data collection—primary and secondary care facilities	June 2026-August 2026	Planned
Phase 2: pilot deployment and data collection—tertiary MTIs^a^	July 2026-November 2026	Planned
Phase 2: qualitative data collection (surveys, interviews, and focus groups)	August 2026-November 2026	Planned
Phase 3: data analysis (quantitative and qualitative)	December 2026-February 2027	Planned
Phase 3: report preparation and policy dissemination	March 2027-April 2027	Planned

^a^MTI: Medical Teaching Institution.

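### A single December 2025-May 2026 comparator does not fit the staggered rollout: it ends a month early for tertiary hospitals starting in July, and the article conflicts on whether June 2026 belongs to their pilot period

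*Protocol article*

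**What the plan says.** The Data Analysis section of the protocol article gives every participating institution the same historical comparator: "Historical referral data from participating institutions covering the 6 months immediately preceding platform deployment (December 2025-May 2026".

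The rollout is not simultaneous. The Results overview describes a phased sequence "beginning with primary and secondary care hospitals and expanding to the 3 tertiary MTIs by July 2026".

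The article describes the period after deployment in two ways. The Methods paragraph of the Abstract has the census run "over a 6-month pilot period commencing June 2026", which is June to November, and the Results overview likewise speaks of six months of collection. The Table 3 row for "pilot deployment and data collection—tertiary MTIs" is dated "July 2026-November 2026", which is five months.

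Table 2 defines bed use as "Proportion of beds occupied at the receiving facilities". Its source is "Platform dashboard+hospital records", and it is analysed descriptively and by a before-after comparison. The article does not say how June 2026 at the tertiary hospitals is to be classified.

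**The concern.** A before-after comparison depends on each facility's time being labelled correctly as before or after go-live. One calendar window does this only if all facilities start together. Here the three tertiary hospitals, which receive the referrals, start later than the facilities that send them.

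Two things are at stake:

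- **The comparator.** June 2026 is the tertiary month closest to go-live, and the only one before go-live that falls within the pilot's June-November calendar. The stated window leaves it out.
- **The post period for bed use.** Hospital records of occupancy exist for June whether or not the platform is running. An analyst who applies the common six-month pilot to them would count a month before go-live as exposed, and a real change in occupancy would look smaller.

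**Working it through.** **Inputs, all from the protocol article.** Comparator December 2025-May 2026 (Data Analysis). Pilot of six months from June 2026 (Abstract; Results overview). Tertiary hospitals live by July 2026 (Results overview). Tertiary deployment and data collection July-November 2026 (Table 3). Bed use drawn partly from hospital records (Table 2). The article gives no baseline occupancy or expected effect, so the effect sizes below are assumptions for illustration.

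**Step 1: reproduce the plan's window.** Six months back from 1 June 2026 is December 2025-May 2026 (182 days). The stated dates are reproduced for a June start.

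**Step 2: apply the same rule to the tertiary hospitals.** Six months back from 1 July 2026 is January-June 2026 (181 days). The stated window starts and ends one month too early for them.

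**Step 3: the post period under each reading, with go-live on 1 July.**

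| | Common pilot, June-November | Table 3, July-November |
|---|---|---|
| Length | 183 days | 153 days |
| Days before go-live | 30 | 0 |
| Share before go-live | 30/183 = 16.4% (1/6 by months) | 0% |
| Where June falls | post period | neither period |
| June used as comparator | no | no |

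**Step 4: attenuation under the common pilot.** If the change is constant after go-live and absent before it:

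observed change = true change × (1 − 30/183) = true change × 0.836

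| Assumed true change in occupancy (percentage points) | Observed |
|---|---|
| 2 | 1.67 |
| 5 | 4.18 |
| 10 | 8.36 |

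**Step 5: sensitivity to the go-live date.** The wording leaves the day open. Under the common pilot, the share of tertiary post time before go-live is:

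- live on 1 June: 0/183 = 0%
- live on 15 June: 14/183 = 7.7%
- live on 1 July: 30/183 = 16.4%
- live on 31 July: 60/183 = 32.8%

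**Step 6: the primary outcomes.** Table 2 takes unnecessary referrals from platform records and the specialist response field, and response time from platform time stamps. The Eligibility Criteria restrict the cohort to records created through the platform. Tertiary activity before the platform cannot enter those post-period data, so the attenuation in Step 4 does not carry over to them.

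**The case against.** The strongest objection concerns an inference a reader might draw: that June at the tertiary hospitals is counted as pilot time, so the bed-use effect is diluted by a sixth. The article does not say this. The Table 3 row covers data collection as well as deployment and starts in July; on those dates June causes no dilution. The common six-month pilot makes pooling possible without stating it. This part of the objection stands, and the dilution is conditional.

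The window can also be defended as internally consistent: if deployment means the first facility's start, its dates are correct, and one common pre-rollout period is a legitimate choice. That holds for the facilities starting in June. It does not make the window the half-year before deployment at hospitals starting in July.

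June may not be a clean control month either. The primary and secondary facilities go live then, and training is scheduled for May, so tertiary June may be partly exposed. This stands. It argues for reporting results both with and without June rather than simply moving June into the baseline.

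The gain is also limited. Bed use is a secondary outcome, and January-June shares no calendar month with July-November, so re-anchoring the window does not remove seasonal confounding.

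Finally, facility-level coding is the kind of detail an article may leave to a fuller document. That is fair for the coding itself. The dates, however, are stated here and do not agree with each other.

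**Conclusion.** The point holds in limited form. For tertiary hospitals starting on 1 July 2026, the fixed window ends one month before go-live, and June 2026 is not comparator data under either reading. The article also conflicts with itself on whether the tertiary post period is six months from June or five months from July.

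The consequence for bed use depends on which reading applies. Under the common June-November period, about one sixth of tertiary post time (16.4% of days) precedes go-live, and a constant change is attenuated to about 84%. Under Table 3, June contributes no dilution and is simply unused. These figures assume a 1 July start, equal weight per day, no effect before go-live and a constant effect afterwards. If June is partly exposed through the referring facilities, the attenuation under the common period would be smaller.

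No dilution of either primary outcome is shown. The issue is worth settling before data collection because it concerns a stated rule, may misclassify exposure, and is cheap to correct.

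**What to change.** 1. Reconcile the six-month pilot from June (Abstract and Results overview) with the July-November tertiary row of Table 3, and state which period applies to the tertiary hospitals.
2. In Data Analysis, replace the single fixed window with a rule tied to each facility's own go-live date: comparator, the six months before that date; post period, from that date on. For a tertiary hospital starting on 1 July, the comparator is January-June 2026.
3. Start the bed-use post period at each receiving hospital's go-live, and code exposure in the regression models by facility go-live date rather than calendar month.
4. Extract the June 2026 registers and bed records at the three tertiary hospitals. Because referring facilities go live in June, report the before-after contrast twice: with June as comparator, and with June excluded as a transition month.

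The cost is a change of wording and one further month of record extraction at three hospitals where historical extraction is already planned. The tertiary post period becomes five months, as Table 3 already has it. No additional patients or procedures are needed.
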